### Participants

Participants will be parents or caregivers of a child with cancer who speak English or Spanish between ages 0 and 18 years. Parents and caregivers of children with cancer must have access to the internet (including access exclusively via cellular data or access via a borrowed institutional device). The only disease-based exclusion criteria are known poor or uncertain prognosis at the time of approach (child not expected to live longer than 6 months). In families with 2 caregivers, both will be eligible to participate in the study, including receiving the intervention and completing study measures; however, 1 caregiver will be asked to identify as the primary participating caregiver at study enrollment.

### Sample Size

Based on the power analyses discussed below, 350 parents and caregivers of children with cancer will be recruited to account for a conservative 25% attrition rate. Of note, although multiple caregivers from each family are eligible to participate, the target sample size of 350 parents and caregivers of children with cancer refers specifically to 350 primary participating caregivers from unique families. Data from nonprimary participating parents will be used only for exploratory analyses. Based on the results from pilot studies, we expect approximately 20% of the 350 families recruited to include a second participating parents and caregivers of children with cancer. Recruitment, retention, and engagement strategies have been an explicit focus of previous eSCCIP research, and strategies generated from this research and the literature inform the recruitment plan [35,36]. Recruitment targets are feasible based on the number of children with cancer treated annually at sites A, B, and C (1000 per year across sites), as well as the number of English-speaking and Spanish-speaking parents and caregivers of children with cancer at each site. We expect 40%-50% of the sample to be Spanish-speaking parents and caregivers of children with cancer. Previous eSCCIP studies have had high recruitment rates (64%-70%) [24,36] as well as retention rates of over 70% in eSCCIP pilot work. Estimating 25% study attrition is an appropriately conservative approach; however, recruitment targets will be evaluated frequently and adjusted accordingly if attrition is higher than expected, given previous work.

To specifically address aim 3, parents and caregivers of children with cancer will be identified from each study site using purposive sampling across demographic groups. We will initially target 10 participants from each site (n=30), comprising 6 parents and caregivers of children with cancer (3 English-speaking and 3 Spanish-speaking), 2 psychosocial providers, and 2 oncology providers, but final recruitment will be dependent upon data saturation. We will complete interviews until no new ideas are shared, consistent with best practices for reaching saturation in qualitative research [37].

### Study Conditions and Delivery

#### eSCCIP Intervention

The content of eSCCIP/eSCCIP-SP has 4 web-based, self-directed cores designed for parents and caregivers of children with cancer to complete over 1 month during their child’s active cancer treatment (including maintenance therapies) or shortly after completion of treatment. Each core is a unique mix of original video content and web-based activities and is complemented by a brief telehealth follow-up with an eSCCIP-trained clinical interventionist (ie, guide). Cores 1-3 include novel content derived directly from evidence-based cognitive behavioral concepts and family system principles modeled from components of the in-person predecessor of eSCCIP; core 4 is designed as a wrap-up core to summarize intervention content. All cores incorporate family systems theory to maintain an interpersonal focus and normalize the family’s experiences. All intervention materials exist in English and Spanish, and telehealth sessions are delivered in English or Spanish, depending on enrollment in eSCCIP or eSCCIP-SP.

Video content falls into two distinct categories: (1) the multifamily video discussion groups, which were initially created for the Surviving Cancer Competently Intervention Program—Newly Diagnosed protocol, consist of recorded and edited conversations between a group of 17 parents and caregivers of children with cancer that serve as a powerful family systems proxy of participants’ interaction with other parents and (2) skill-building videos, where foundational cognitive behavioral intervention skills, such as cognitive reframing, are introduced. The multifamily video discussion groups capture themes common among parents and caregivers of children with cancer (eg, anger, guilt, and emotional exhaustion), examples of coping (eg, putting things in perspective), and the impact on the family over time (eg, siblings, grandparents, and thinking about the future). The skill-building videos feature interviews with parents and providers, as well as graphics and narration illustrating foundational intervention skills. Web-based activities provide opportunities for caregivers to practice the skills they have learned.

All web-based activities are securely captured by the program, allowing the guide to view data entered by participants (eg, free text responses) and integrate participant responses into telehealth follow-up sessions. The telehealth follow-ups after cores 1-3 are the only component of eSCCIP that is scheduled with a trained guide. The telehealth follow-up sessions follow a flexible manualized format to ensure standardization across guides and appropriate delivery of key intervention principles.

#### Education Control

Parents and caregivers of children with cancer randomized to the patient education control condition will be given a unique log-in to access a website with information about psychosocial functioning, coping, and PTSS related to pediatric cancer. This website will be available in both English and Spanish and will consist of information modified from CopingSpace [38], an evidence-informed website developed by Ryan’s Case for Smiles, a national organization dedicated to supporting families impacted by pediatric cancer and other chronic diseases. Topics include age-appropriate explanations and coping strategies for children, the siblings’ unique experience and needs, warning signs a child is not coping well, techniques to reduce your stress and anxiety, and practical tips for managing meals and family needs. Unlike eSCCIP/eSCCIP-SP, the education control website will not include instruction in the cognitive behavioral skills taught in eSCCIP/eSCCIP-SP nor will it include access to the videos or telehealth follow-up sessions in eSCCIP/eSCCIP-SP. The high-quality information provided to parents and caregivers of children with cancer makes this a valuable and meaningful comparator condition.

### Study Platform

The eSCCIP/eSCCIP-SP and education control programs have been built in the most recent version of the Research Infrastructure Containing e-interventions system developed and maintained by the University of Virginia Center for Behavioral Health and Technology. This platform provides the tools to both deliver robust digital health interventions as well as to manage participants in research trials. The system is designed to support projects that contain protected health information and are subsequently subject to compliance with federal and state regulations regarding data of this type. eSCCIP/eSCCIP-SP has been designed to be delivered as a fully automated program, but also it has the functionality to incorporate human support components (eg, facilitate communication between participant and guide). It includes 4 cores and 3 telehealth visits, with the cores automatically made available to the participant over time. After completion of the first core, the first telehealth visit is scheduled for a time in the upcoming week. The second and third cores are available 1 week after the completion of the previous core and include a subsequent telehealth visit. The fourth and final core concludes the intervention with a review of the program. Participants access the intervention through a secured portal, and all data are captured and maintained consistent with Health Insurance Portability and Accountability Act’s guidelines.

### Study Procedure

Potential participants will be screened for eligibility using a brief, web-based screening questionnaire that is accessible by direct contact with a member of the study team or through the study interest website. Once screened, an RC will confirm eligibility and instruct participants about the consent process. Web-based consent procedures will be conducted via DocuSign or a similar secure software. Once web-based consent is complete, participants will receive a unique username and password to log onto their randomized condition (eSCCIP/eSCCIP-SP or education control). Study questionnaires will be completed through this web platform. As there are no required components of the education control, automated or RC-directed text and email reminders to use the program will not be required for individuals randomized to the education control.

After completion of the initial web-based assessment battery, participants in the intervention condition will schedule their initial telehealth session using an automated scheduling tool available through the platform hosting eSCCIP/eSCCIP-SP. Participants will be notified that the overview core and core 1 need to be completed prior to the telehealth session. Automated reminders will be sent at regular intervals to encourage participation in study cores. Manual follow-up by RCs will also be initiated in cores that are not completed. Cores will automatically unlock at 1-week intervals, and telehealth sessions will be scheduled directly with the participant. A total intervention completion window of 4-6 weeks will be anticipated by the study team for each participant, building in some additional time for start-up and potential scheduling delays. A similar process has been successfully implemented in eSCCIP pilot studies [24,30]. Because eSCCIP/eSCCIP-SP cores and the education control website are delivered digitally, all parents and caregivers of children with cancer will have convenient access to their respective condition’s content anywhere the internet is available.

### Treatment Fidelity

The administrative interface of the intervention platform collects several metrics that will be used to record the intervention and monitor participation, including generating a comprehensive activity record of core use (ie, a record of completion of each activity and a record of all free-response answers). Fidelity checklists and session outlines have also been developed for the telehealth follow-up sessions. The designated Fidelity Consultant, a pediatric psychologist with extensive experience delivering psychosocial intervention to families, will watch and code 15% of all telehealth sessions for each guide using the fidelity checklists as a measure of treatment fidelity to strengthen study rigor.

### Study Outcomes

Data will be collected at 3 time points: prior to beginning the intervention (T1), postintervention (after 6 weeks; T2), and at 3-month follow-up (3 months after baseline; T3). Outcome measures include the Psychosocial Assessment Tool (PAT) [39,40], the Multidimensional Scale of Perceived Social Support [41], the Kessler Psychological Distress Scale (K-6) [42,43], the COVID-19 Exposure and Family Impact Scale [44], the Coping Self-Efficacy Scale [45], the Cognitive Emotion Regulation Questionnaire [46], Distress Thermometer [47], the Patient-Reported Outcomes Measurement Information System Short Form (PROMIS Short Form v1.0—Anxiety-8a) [48], the posttraumatic stress disorder checklist [49], as data on previous psychosocial service usage. Individuals randomly assigned to the intervention condition will also complete a questionnaire at T3 measuring satisfaction and acceptability with the intervention, which has been used in all prior eSCCIP studies. Measure description and schedule for data acquisition are provided in Table 1.

**Table 1 table1:** Outcome measures and assessment timing schedule.

Domain or measure	Description	T1^a^	T2^b^	T3^c^
Chart review	Review of patient medical record			
Demographic variables of parents and caregivers of children with cancer	Demographic variables of enrolled parents and caregivers of children with cancer	✓		
Previous psychosocial service usage	Questionnaire to measure contact and work with social work, psychology, psychiatry, pastoral care, community, and hospital-based services for all members of the family	✓	✓	✓
PAT^d^	Brief parent report screener of psychosocial risk [39,40]	✓		
MSPSS^e^	Questionnaire to measure perceived social support from family, friends, and significant other [41]	✓	✓	✓
K-6^f^	Questionnaire to measure acute distress [42,43]	✓	✓	✓
CEFIS^g^	Questionnaire to measure the extent to which a family has experienced or been “exposed” to COVID-19–related potentially traumatic events (eg, economic changes, illness in family) and the impact of these events on the family’s functioning and well-being [44]	✓	✓	✓
CSES^h^	Questionnaire to measure the perceived ability to cope effectively with challenging situations across 3 domains (use problem-focused coping, stop unpleasant emotions and thoughts, and get support from friends and family) [45]	✓	✓	✓
CERQ^i^	Questionnaire to identify cognitive coping strategies used after a negative event or situation. Measures of 9 different cognitive coping strategies [46]	✓	✓	✓
Distress thermometer	Single-item indicator of psychosocial distress that is widely used in the oncology literature [47]	✓	✓	✓
PROMIS^j^ Short Form v1.0—Anxiety-8a	Questionnaire measuring symptoms of anxiety [48]	✓	✓	✓
PCL-5^k^	Questionnaire to assess for symptoms of posttraumatic stress disorder in the civilian population [49]	✓	✓	✓
eSCCIP^l^ Evaluation Questionnaire	Questionnaire to measure intervention acceptability		✓	✓

^a^T1: preintervention (baseline).

^b^T2: postintervention (after 6 weeks).

^c^T3: follow-up (3 months after baseline).

^d^PAT: Psychosocial Assessment Tool.

^e^MSPSS: Multidimensional Scale of Perceived Social Support.

^f^K-6: Kessler Psychological Distress Scale.

^g^CEFIS: COVID-19 Exposure and Family Impact Scale.

^h^CSES: Coping Self-Efficacy Scale.

^i^CERQ: Cognitive Emotion Regulation Questionnaire.

^j^PROMIS: Patient-Reported Outcomes Measurement Information System.

^k^PCL-5: posttraumatic stress disorder checklist.

^l^eSCCIP: Electronic Surviving Cancer Competently Intervention Program.

### Power Analyses and Sample Size Consideration

The primary end point of the study is to compare posttest differences in distress post intervention between intervention and education control groups. In a recent pilot study of 14 participants, we detected a mean change of 1.71 (SD 2.09) in distress on the distress thermometer at 1 month in the English version of the questionnaires. In standardized form, the effect size is 0.82. We do not have an estimate of the impact of the education control group on our primary end point; however, we expect no more than a modest to medium effect (0.2 to 0.5). Therefore, we are planning a sample size to detect a difference in effects between the groups of at least 0.3. Power analyses based on the analysis of covariance (ANCOVA) model and assuming a correlation of at least 0.5 between pretest and posttest scores suggest that a sample size of 350 individual parents and caregivers of children with cancer (175 in each group) can detect a difference of ≥0.3 in standardized mean distress reduction between intervention and education group conditions with a power of at least 80% at the level of significance of .05 and assuming an attrition rate of 25%. Therefore, a sample size of 350 is planned for this study.

### Data Quality

Data quality will be monitored throughout intervention implementation and data collection. The research team will routinely generate data quality reports (via built-in functionality) and meet biweekly to review the reports, discuss any identified issues (eg, missing data), and outline remedial actions. For the education control website, data from CopingSpace.org will be migrated to the same server that will host eSCCIP/eSCCIP-SP for ease of tracking and standardization. Once data collection is complete, a rigorous data cleaning, description, and covariate screening process will be carried out prior to analysis. Data will be first inspected for erroneous, outlying, or potentially high-leverage values, and missing data patterns tabulated and visualized. Data from the 3 recruiting study sites will then be pooled for analyses in 2 different versions of the data set separating participants who provide data for at least 1 measurement visit from participants who provide data at all time points. Multiple imputations will be used to handle missing data, including determination of a primary missing data mechanism, appropriate selection of auxiliary variables (if applicable), and sensitivity analyses to check for robustness of underlying assumptions (eg, MNAR selection models, pattern mixture models) [50]. Efficacy analyses will be carried out for both sets, thus providing a complete picture of whether and how missing data impact analysis results.

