**Methods:**

Using a randomized controlled clinical trial design, 350 eligible parents and caregivers of children with cancer will be randomly assigned to the intervention (eSCCIP/eSCCIP-SP) or an education control condition. Data will be collected at 3 time points: preintervention (prior to randomization), immediately post intervention (after 6 weeks), and at a 3-month follow-up (from baseline). Participants randomized to either condition will receive study material (eSCCIP/eSCCIP-SP intervention or education control website) in English or Spanish, based on the primary language spoken in the home and participant preference.

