### Planned Statistical Analyses

#### Aim 1: Analyses

The primary end point of specific aim 1 is the change in acute distress as measured by the K-6 distress scale over 1 month (immediately post intervention). To test whether eSCCIP/eSCCIP-SP is more efficacious in decreasing acute distress relative to the education control (hypothesis 1), an ANCOVA model will be estimated, which has repeatedly been shown to provide optimal estimate precision, power, and CI coverage among pretest-posttest analysis alternatives in RCTs [51,52]. The ANCOVA model will be used to test for group differences in K-6 distress scores, controlling for preintervention distress scores. Covariates will be incorporated if baseline differences are identified across site-specific, program delivery, and demographic variables. As participants may be nested within providers at each site, we will explore the need for specifying a mixed-effects model, contingent upon the size of the provider effect (eg, design effect, impact on model standard errors) and the number of providers available in the data set. With regard to families with 2 participating parents and caregivers of children with cancer, methodological research has shown poor model performance of mixed-effects dyadic models if the proportion of singletons (dyads with only 1 member) is high, as is expected for this study; therefore, primary analyses will be conducted only on primary participating caregivers [53]. We do not expect treatment effects to differ by dyad status and will test this assumption with data obtained from nonprimary participating parents analyzed in exploratory analyses. Model assumptions will be checked and alternative robust will be methods used, for instance, robust SEs, bootstrapping, or generalized linear models, if applicable [54,55]. Secondary end points (eg, PTSS and anxiety) in specific aim 1 will be analyzed in the same manner. All tests will be 2-tailed at a .05 level of significance; the Benjamini-Hochberg method will be used to adjust for multiple testing [56].

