#### Aim 2: Analyses

Specific aim 2 analyses will further probe the eSCCIP/eSCCIP-SP user experience, intervention effects, and boundary conditions. First, descriptive summaries and data visualizations will be used to explore user engagement variables, such as the number of cores completed. Next, potential risk and protective factors will be examined by introducing interaction effects to the models previously described for specific aim 1, including all primary and secondary end points. Interaction terms will be formed between intervention assignment and each potential moderator variable, tested in separate models under the Benjamini-Hochberg control method. Follow-up inferential and graphical procedures will be used to interpret significant interaction effects [57]. Variables selected as potential moderators are participant characteristics guided by the Behavior Change Model for Internet Interventions (eg, race, gender, and socioeconomic status) and family risk variables guided by the Pediatric Preventative Health Model (eg, COVID-19 Exposure and Family Impact Scale score, PAT baseline score). Of primary importance is the potential moderating effect of intervention language, which will similarly be tested. Additional exploratory analyses will be carried out to answer key auxiliary questions and maximize the use of the data collected. First, we will examine any possible persisting effects of eSCCIP/eSCCIP-SP at the 3-month follow-up time point, based on longitudinal analysis models designed for randomized pretest-posttest-follow-up designs [58]. Similarly, we will also explore whether treatment effects differed between parents and caregivers of children with cancer from families with 1 or 2 participating caregivers, as well as examine trends in data provided by nonprimary participating caregivers.

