
### Limitations

It is possible that the sample of parents and caregivers of children with cancer who opt to participate in our research are self-selected and may not fully represent the population of caregiving individuals of children with cancer. To identify and more broadly implement successful recruitment, retention, and engagement strategies, the primary study team recently published a manuscript describing qualitative data from focus groups and interviews [36]. The sample included past eSCCIP participants and parents and caregivers of children with cancer who were naïve to eSCCIP (but viewed some intervention content prior to participating). By implementing these strategies broadly over the course of the study, a wide range of potentially eligible parents and caregivers of children with cancer will be targeted for inclusion. We will monitor recruitment and enrollment rates closely over the course of the study, adjusting recruitment strategies if indicated. It is also possible, given both the duration of the study follow-up and randomization procedures, that participants may drop out or be lost to follow-up. Efforts by research staff to maintain participation in the study and to obtain postintervention measures for all participants will be made, including participants providing multiple means of contact to aid in follow-up as well as receiving study payments after completion of each data collection time point. In eSCCIP development trials, close tracking and monitoring procedures led to high retention rates for participants who begin the intervention, and the addition of automated reminders and a stepped care approach to communicate with participants will bolster these efforts. The characteristics of completers versus noncompleters will also be examined for systematic differences, and we will use an intent-to-treat design for data analyses.

Second, since the intervention involves an active intervention component, including telehealth follow-up with a trained guide for participants allocated to eSCCIP/eSCCIP-SP, blinding of guides is not possible. However, study team members not involved in intervention delivery will not have access to random assignment information. After randomization, participants will be instructed on the procedures within their assigned group. All outcome measures will be completed directly on the internet by study participants, further reducing the risk of bias.

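### The completer data set requires the 3-month visit although the primary K-6 endpoint uses only baseline and post-intervention scores, and its rank against the larger set is not stated

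*Protocol article*

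**What the plan says.** The Data Quality section of the protocol article pools the three sites into two versions of the data set, separating "participants who provide data for at least 1 measurement visit from participants who provide data at all time points". The second set is contained in the first. On missing values it says: "Multiple imputations will be used to handle missing data, including determination of a primary missing data mechanism", with sensitivity analyses for data missing not at random. It closes: "Efficacy analyses will be carried out for both sets, thus providing a complete picture of whether and how missing data impact analysis results". Neither this section nor Aim 1: Analyses says which set decides the primary hypothesis. The Limitations section adds that "we will use an intent-to-treat design for data analyses", without linking this to either set.

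Study Outcomes sets the visits as "prior to beginning the intervention (T1), postintervention (after 6 weeks; T2), and at 3-month follow-up (3 months after baseline; T3"). Aim 1: Analyses defines the primary endpoint as the "change in acute distress as measured by the K-6 distress scale over 1 month (immediately post intervention"), analysed by ANCOVA on the baseline score; secondary endpoints follow the same method. T3 enters under Aim 2: Analyses, among additional exploratory work: "we will examine any possible persisting effects of eSCCIP/eSCCIP-SP at the 3-month follow-up time point".

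**The concern.** The primary analysis compares K-6 at T2, adjusted for K-6 at T1. Whether someone returns at T3 has no bearing on whether that outcome was observed. A set that demands all three visits nevertheless drops anyone with T1 and T2 but no T3.

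Three things follow for the completer analysis:

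- Observed primary outcomes are left out, and precision falls.
- The comparison is restricted to people who stayed until 3 months. That is a post-randomisation event and may differ by arm: the intervention arm has guide sessions, automated reminders and coordinator follow-up on unfinished cores, while program reminders are not required in the control arm.
- The check misses its declared aim. A difference between the two sets mixes loss of the primary outcome (no T2) with loss of a later visit (no T3), so it cannot be read as the effect of missing primary data.

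Because the two sets are not ranked, the text shown also leaves unsaid what happens if they disagree.

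**Working it through.** **Which visits each element needs**

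| Element | T1 | T2 | T3 |
|---|---|---|---|
| Primary endpoint (Aim 1: Analyses) | yes | yes | no |
| Persistence of effect, exploratory (Aim 2: Analyses) | yes | yes | yes |
| All-time-points set (Data Quality) | yes | yes | yes |

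The all-time-points set matches the exploratory analysis, not the primary one.

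**The plan's own sample size**

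Inputs from Power Analyses and Sample Size Consideration: standardised difference d = 0.3, pre-post correlation ρ = 0.5, significance level 0.05 (two-tailed under Aim 1: Analyses), power 80%, attrition 25%.

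n per arm = 2(z₀.₉₇₅ + z₀.₈₀)²(1 − ρ²)/d² = 2 × 7.849 × 0.75/0.09 = 130.8, rounded up to 131.

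Allowing for attrition: 131/0.75 = 174.7, rounded up to 175 per arm, 350 in total. This reproduces the plan, so the sample size is not in question.

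Power at n per arm = Φ(d√(n/2)/√(1 − ρ²) − 1.960). At n = 131: 0.3 × 8.093/0.866 = 2.804, and Φ(0.844) = 80.1%.

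**Cost inside the completer set**

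Assume first that the 25% attrition is loss by T2, so 350 × 0.75 = 262.5 participants (about 131 per arm) have the primary outcome and 87.5 do not. Let a share m of those seen at T2 then miss T3. The documents give no value for m; the values below are assumptions, taken equal in both arms and unrelated to outcome.

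- Observed outcomes left out = 262.5 × m
- Completers per arm = 131.25 × (1 − m)
- Share of all exclusions due to T3 alone = 262.5m/(87.5 + 262.5m)

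| m (assumed) | Observed primary outcomes left out | Completers per arm | Power | Exclusions due to T3 alone |
|---|---|---|---|---|
| 0% | 0 | 131 | 80.1% | 0% |
| 5% | about 13 | 125 | 78.1% | 13% |
| 10% | about 26 | 118 | 75.9% | 23% |
| 20% | about 52 | 105 | 70.9% | 38% |

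The last column shows how far the comparison of sets is contaminated by a visit the endpoint does not use.

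**The other reading of the attrition figure**

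If the 25% already covers loss through T3, completers number about 131 per arm with 80.1% power. Some observed outcomes are still left out unless all loss occurs by T2. For example, with 80% seen at T2 (assumed), 350 × (0.80 − 0.75) = 17.5 participants are dropped, and the T1+T2 set of 140 per arm would have 82.6% power against 80.1%.

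**The case against.** The strongest reply is that the completer analysis is an addition. Nobody leaves the larger set, so no observed outcome is lost to the trial. The Data Quality section presents the pair of sets as a check on missing data, and multiple imputation for missed visits has work to do only in the at-least-1-visit set. The abstract places baseline collection as "preintervention (prior to randomization), immediately post intervention (after 6 weeks), and at a 3-month follow-up (from baseline"), so that set is in effect everyone randomised and fits the intent-to-treat statement. All of this stands. One caveat: Study Procedure can be read as placing the baseline battery after log-on to the assigned condition, in which case the larger set could miss a few randomised participants.

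It is also fair to say that a formal ranking of analysis sets is ordinary SAP content and that this is a condensed article. The missing ranking alone would therefore not be a finding. The stated requirement of T3 is different: it is a rule the article fixes.

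A reader might infer more: that the two sets are co-equal routes to success. If significance in either set counted, and the larger set were a complete-case T1+T2 sample, the two-sided type I error would be about 6.0% to 7.1% when completers are 95% to 80% of it. The documents do not support that reading. No sentence gives an either-set rule, the stated purpose is a robustness check, and imputation is planned in the larger set.

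On differential retention, the reminders in Study Procedure concern program use rather than assessments. The Limitations section promises efforts to obtain post-intervention measures from all participants, several means of contact, payment after each time point, and a comparison of completers with noncompleters. Selection by arm is thus possible but not shown.

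**Conclusion.** The concern holds for the completer analysis. The article plans efficacy analyses in a set defined by a visit that the primary endpoint does not use. That set omits participants with an observed primary outcome, conditions on later retention, and blurs the question it is meant to answer. Its subordinate rank can be inferred but is not stated.

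The size is modest and conditional on T3-only loss, which the documents do not give. It ranges from no power cost, if nobody seen at T2 misses T3, to a fall from 80.1% to 70.9% if 20% do, on top of 25% lost by T2. If the 25% runs through T3, the completer set keeps about 80%. These figures concern the completer set only; the power of the intent-to-treat analysis and the planned 350 are unaffected.

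**What to change.** Amend the Data Quality section in three respects:

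1. State that the single primary analysis is the ANCOVA in all randomised primary caregivers, with multiple imputation. K-6 at T3 may serve as an auxiliary variable, which also makes use of the later visit.
2. For the primary and secondary T2 endpoints, replace the all-time-points set with participants who have the relevant measure at both T1 and T2. Label it a sensitivity analysis that does not decide the hypothesis.
3. Keep the planned analyses for data missing not at random. Reserve the all-time-points set, if wanted, for the exploratory T3 analyses.

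This takes two or three sentences, needs no new data and adds no analysis. It brings the section into line with the intent-to-treat commitment under Limitations. It should be settled before outcome data are seen.
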